### Statistical Analyses

#### Feasibility-Related Analyses

Descriptive statistics of feasibility measures such as adherence, dropouts, and recruitment will be estimated and provided. Bias-corrected bootstrap CIs of the Spearman correlation between baseline and 6-month assessment will be reported. For participants identified through the i2b2 system at UAB Health System, we are tracking the following: (1) no response, (2) screened but failed, (3) screened as eligible but did not consent, (4) screened as eligible and consented, (5) enrolled but withdrew before the intervention started, (6) started the intervention but withdrew during the study, and (7) completed the intervention and final data collection. In addition to the descriptive measures of recruitment outcomes, we will run at least a binary logistic regression model to explore and predict factors associated with successful recruitment outcomes. Successful recruitment will be defined as participants screened as eligible, consented to participate, completed the intervention, and completed the final data collection. Age, gender, race, location status (urban vs nonurban), and health insurance status will be covariates.

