**Process**		
	Time taken to recruit	Time from study activation to enrollment of the last participant
	Recruitment rate	Number of participants enrolled per recruitment time period
	Retention rate	Percent of participants completing the trial
	Enrollment rate	Enrolled of eligible or approached
	Decline rate	Percent of eligible individuals who declined participation
	Completion rate	Percent of enrolled participants who completed the study
	Protocol adherence	Total number of sessions attended of the total 24 coaching sessions; number of monitoring calls answered
	Challenges in collecting blood samples using LabCorp	Qualitative data from patients
	Time to complete data collection	Time to complete pre- and postdata collection
	Duration of human coaching	Time to schedule and conduct orientation and diabetes education
	Data entry errors	Data entry errors
	Percent missing data	Percent missing data

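### The definition of successful recruitment also requires completing the study, so the exploratory recruitment model mixes recruitment with retention and conflicts with Table 3

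*Protocol article*

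**What the plan says.** Under Feasibility-Related Analyses, the protocol article lists seven statuses that are tracked for people identified through the health-system database, from no response (1) to completion of the intervention and final data collection (7). It then plans a regression: "we will run at least a binary logistic regression model to explore and predict factors associated with successful recruitment outcomes". The outcome is fixed in the next sentence: "Successful recruitment will be defined as participants screened as eligible, consented to participate, completed the intervention, and completed the final data collection". The adjustment set follows: "Age, gender, race, location status (urban vs nonurban), and health insurance status will be covariates".

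Two of the tracked statuses describe people who were recruited and then left: "5) enrolled but withdrew before the intervention started, (6) started the intervention but withdrew during the study".

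Table 3 draws the lines differently. Recruitment rate is "Number of participants enrolled per recruitment time period" and enrollment rate is "Enrolled of eligible or approached". Retention rate is "Percent of participants completing the trial" and completion rate is "Percent of enrolled participants who completed the study". The Outcomes section likewise names recruitment and retention as separate primary feasibility indicators.

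**The concern.** Under the stated rule only status 7 counts as success. Someone who was eligible, consented, was enrolled and then withdrew (status 5 or 6) falls into the failure group with those who were never recruited. Table 3 would count the same person as recruited and, separately, as not retained.

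This is the only model the article specifies for recruitment factors, and the Principal Findings section says the study should help identify changes that improve recruitment. Recruitment problems and retention problems call for different remedies. A covariate that affects only completion would show up in this model as a recruitment factor, and one that affects the two in opposite directions could be diluted or reversed.

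**Working it through.** **1. Which statuses count as success**

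| Status | Feasibility-Related Analyses | Table 3 |
|---|---|---|
| 5, withdrew before the intervention | failure | enrolled, not retained |
| 6, withdrew during the study | failure | enrolled, not retained |
| 7, completed | success | enrolled, retained |

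The two sections disagree on statuses 5 and 6.

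**2. Inputs**

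- Randomized: 88 (Sample Size Justification).
- Planned attrition: 15% (same section). As a check that this figure drives the plan's own calculation, take N = 74 (88 × 0.85 = 74.8, rounded down), r = 0.5, two-sided alpha 0.05, 80% power and noncentrality d√N / (2√(1 − r²)). The noncentral t gives d = 0.572, as the article states.
- Possible denominators (Results): 1938 phone contact attempts, 1192 people phone-screened, 162 potentially eligible and consented to HbA1c screening. The article does not say which group enters the model, and 1938 counts attempts, which need not be persons.

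The article gives no figure for the recruitment model itself, so there is none to reproduce.

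**3. How many are miscoded**

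Enrolled dropouts = 88 × 0.15 = 13.2; successes under the stated rule = 88 − 13.2 = 74.8. At an assumed 5% or 25% attrition the dropouts would be 4.4 or 22.

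Share of the failure group = 13.2 / (D − 74.8):

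- D = 1938: 13.2 / 1863.2 = 0.7%
- D = 1192: 13.2 / 1117.2 = 1.2%
- D = 162: 13.2 / 87.2 = 15.1%

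**4. What this does to an odds ratio**

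P(success) = P(enrolled) × P(completed given enrolled). Take a binary covariate split 50/50, with average enrolment 88/D. The completion rates by covariate level are assumptions that average 85%; the documents give none.

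Worked case, no effect on enrolment (OR 1.0), completion 75% versus 95%:

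- D = 1192: enrolment 88/1192 = 0.0738 at both levels. Success is 0.0738 × 0.75 = 0.0554 versus 0.0738 × 0.95 = 0.0701. Odds are 0.0586 and 0.0754, so OR = 0.78.
- D = 162: enrolment 88/162 = 0.543. Success is 0.407 versus 0.516. Odds are 0.6875 and 1.066, so OR = 0.64.

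Odds ratios under the stated definition:

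| Enrolment OR | Completion by level | D = 1938 | D = 1192 | D = 162 |
|---|---|---|---|---|
| 1.0 | 85% / 85% | 1.00 | 1.00 | 1.00 |
| 1.0 | 80% / 90% | 0.88 | 0.88 | 0.80 |
| 1.0 | 75% / 95% | 0.78 | 0.78 | 0.64 |
| 1.0 | 95% / 75% | 1.28 | 1.29 | 1.55 |
| 1.5 | 85% / 85% | 1.50 | 1.49 | 1.41 |
| 1.5 | 80% / 90% | 1.32 | 1.32 | 1.13 |
| 1.5 | 75% / 95% | 1.17 | 1.16 | 0.91 |
| 1.5 | 95% / 75% | 1.91 | 1.92 | 2.20 |

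If completion does not depend on the covariate, the enrolment odds ratio survives almost intact at the large denominators and is mildly attenuated at 162. If completion does depend on it, the coefficient moves, and this outcome alone cannot show which process moved it.

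**The case against.** Five points can be made for the plan.

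- **The model is exploratory and supplementary.** It runs in addition to descriptive measures that Table 3 defines separately, and no primary outcome or decision rule depends on it. This stands and limits the harm.
- **There may be few or no dropouts.** The abstract reports 88 enrolled with data collection complete, and the Results say that the 88 randomized have completed the 6-month follow-up. Read literally, almost nobody is miscoded. The sentence could also mean that the follow-up period has ended. The definition separately requires completing the intervention, and Recruitment and Retention provides for classifying unresponsive participants as lost to follow-up. The point stands as a possibility.
- **Other models are left open.** The text promises at least one binary model, and the seven statuses would support others. True, but the one outcome it does define is the one at odds with Table 3.
- **The composite can be read as end-to-end yield.** Who moves from contact to usable month-6 data is a fair question for a pilot. It is a different question from who is recruited, and needs its own name.
- **A full retention model is not a sound substitute.** The five listed covariates plus the two randomized factors need at least seven slopes for about 13 events, fewer than two per slope. If all 88 completed, it cannot be fitted. This stands and shapes the fix.

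A reader might also infer that the model is uninformative about recruitment, or that the randomized rewards and coaching confound it. The first goes too far: with 1192 or more in the denominator about 99% of failures are genuine non-recruits. The second does not follow: allocation is random with equal probability, so arm is independent in expectation of age, gender, race, location and insurance.

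**Conclusion.** The inconsistency is real. A stated rule codes enrolled participants who withdrew as recruitment failures, while Table 3 counts them as recruited and measures their retention separately. The resulting coefficients mix the two processes.

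The size depends on three things the article leaves open: actual dropout, the denominator, and whether completion varies with the covariates. At 15% attrition about 13 of 88 are miscoded. The effect is small at a denominator of 1192 or more unless completion varies with the covariate, larger at 162, and possibly near nil if all 88 completed. The shifts in the table rest on assumed completion rates and are illustrations, not forecasts.

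The documents do not support the stronger conclusions that the model can say nothing about recruitment or that the primary feasibility results are compromised. The change is still worth making: it costs almost nothing, and the definition could otherwise carry over to the optimization trial.

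**What to change.** - Define successful recruitment as consented and enrolled, in line with Table 3. Statuses 5, 6 and 7 then all count as success; for status 4, say whether someone who consented but was not enrolled counts.
- State the model's denominator in persons, for example all those contacted or all those screened eligible.
- If the present composite is kept, report it separately as end-to-end yield.
- Report retention among the 88 randomized descriptively. Add a model only if there are enough dropouts, and keep it small or penalized.

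The cost is one redefinition and at most one extra exploratory regression. The tracked statuses already hold the data.

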#### Analytic Strategy for Preliminary Effectiveness Analyses

We will also estimate effect sizes as preliminary effectiveness estimates. All statistical analyses will follow an intent-to-treat approach. In line with a pilot study, we will also report 75% and 85% CI estimates in addition to the traditional 95% CIs to further aid in the statistical interpretation of the findings [65]. We will use linear mixed models to estimate effects by accounting for correlated data and benefit from the maximum likelihood estimation procedure that uses all information in the dataset in the presence of missing outcome data. Our overall approach will be similar to Pellegrini et al [38]. To evaluate the main effect of each component on pre-post differences in outcomes, we will use baseline as the reference cell to determine differences in change across time (ie, 6 months vs baseline) [38]. However, these effects will be statistically modeled as component-by-time interactions, with the 6-month outcome as the primary end point. We will also include two-way interactions between components (eg, Factor 1 by Factor 2 by time interaction). We will then identify all the active components or combinations of components, where active is operationalized as a mean reduction of 0.5 units (%) in HbA_1c_ between baseline and month 6 [66,67]. Similar analyses will be done for secondary outcomes. Where information related to minimally clinically important differences is available, we will use it to assess whether the combination is active. For example, an average 5% weight loss is considered to be active in the case of weight. We will leverage the generalized linear modeling framework and resampling-based approaches for nonnormal outcomes. We will conduct exploratory analyses to assess biases in the self-reported PROs. While we are not statistically powered to do mediation or moderation analyses, in line with the MOST Preparatory Phase, we will conduct exploratory mediation and moderator analyses using our tracking data as potential mediators or moderators.

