We also present power calculations of our experiment based on our sample size of 88. Assuming a type 1 error rate of 0.05, a conservative pre-post correlation of 0.5 in ANCOVA, and an attrition rate of 15%, we will have 80% power to detect an effect size (Cohen *d*) of 0.572 in our primary outcome. This would imply a main effect difference of 0.86% units of HbA_1c_, assuming an SD of 1.5% [63]. Even if we assume the pre-post correlation is 0.3, which is very conservative, we will have 80% power to detect an effect size of 0.63 for the main effect. Assuming a more realistic pre-post correlation of 0.7, we can detect an effect size of 0.472. Missing outcomes data will be imputed using maximum likelihood estimation or a multiple imputation procedure, and primary analyses will not be restricted to only completers. Hence, our proposed study sample size of 88 participants is powered to detect an even smaller effect size than suggested here since the effective sample size, even assuming an attrition of 15%, would be between 74 and 88. Thus, our pilot study is well-powered to detect moderate to medium effect sizes. These power calculations were done using the MOST package in R (R Core Team), developed by Dziak et al [64].

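### The stated detectable effects belong to an ANCOVA, but the planned model tests component-by-time interactions; unless baseline means are constrained equal, power at those effects is about 64% to 74% with 15% attrition, not 80%

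*Protocol article*

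**What the plan says.** The Sample Size Justification bases its power statement on "a conservative pre-post correlation of 0.5 in ANCOVA", a type 1 error rate of 0.05 and 15% attrition from 88. It gives 80% power at d = 0.572, translated to 0.86% HbA1c with an SD of 1.5%. For a correlation of 0.3 it says "we will have 80% power to detect an effect size of 0.63 for the main effect", and for 0.7 it gives 0.472. It then argues that even smaller effects are detectable, because incomplete cases stay in the analysis and the effective sample size lies between 74 and 88.

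The Analytic Strategy for Preliminary Effectiveness Analyses does not plan an ANCOVA. It plans linear mixed models fitted by maximum likelihood to evaluate each component's effect on pre-post differences: "we will use baseline as the reference cell to determine differences in change across time". It adds that "these effects will be statistically modeled as component-by-time interactions, with the 6-month outcome as the primary end point", and includes a term for Factor 1 by Factor 2 by time. It mentions neither baseline as a covariate nor a constraint on baseline means.

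**The concern.** ANCOVA and a difference in change use the baseline value differently. With unit SD and pre-post correlation ρ, the variance per participant scales with 1 − ρ² under ANCOVA and with 2(1 − ρ) for a change score. The ratio is 2/(1 + ρ), which is 1.54, 1.33 and 1.18 at ρ = 0.3, 0.5 and 0.7. A component-by-time interaction in a mixed model, with component means free at baseline, estimates the difference in change. Power figures derived for ANCOVA would then be too favourable.

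The article says that the pilot is to supply effect sizes and design parameters for a later optimization trial. The less efficient model would widen the confidence intervals of those estimates and let chance baseline imbalance, at 22 participants per condition, enter the component contrasts.

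**Working it through.** **Inputs.** All come from the Sample Size Justification: α = 0.05 (sidedness not stated; two-sided reproduces the figures), 80% power, 44 per level of each factor, 15% attrition (88 × 0.85 = 74.8; 74, or 37 per level, reproduces the figures), SD 1.5%, and ρ = 0.3, 0.5 and 0.7. Effects are in SD units. Power uses the noncentral t distribution. Detectable d is a multiplier times the SE: 2.841 with 70 df and 2.834 with 84 df.

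**1. The article's figures, as ANCOVA.** SE = √[2(1 − ρ²)/37].
- ρ = 0.5: √(2 × 0.75/37) = 0.2013; × 2.841 = 0.572; × 1.5 = 0.86% HbA1c.
- ρ = 0.3: √(2 × 0.91/37) = 0.2218; × 2.841 = 0.630.
- ρ = 0.7: √(2 × 0.51/37) = 0.1660; × 2.841 = 0.472.

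All three stated figures are reproduced.

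**2. Component-by-time contrast, component means free at baseline, 37 followed up and 44 baselines per level.** Maximum likelihood uses the baselines of dropouts. The estimated change in a level is the baseline-adjusted month-6 mean of those followed up minus (1 − ρ) times the mean of all baselines, so SE = √{2[(1 − ρ²)/37 + (1 − ρ)²/44]}.
- ρ = 0.5: √[2(0.02027 + 0.00568)] = 0.2278; × 2.841 = 0.647; × 1.5 = 0.97% HbA1c.
- ρ = 0.3: √[2(0.02459 + 0.01114)] = 0.2673; × 2.841 = 0.759.
- ρ = 0.7: √[2(0.01378 + 0.00205)] = 0.1779; × 2.841 = 0.505.

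Against step 1, the SE is larger by a factor of 1.13, 1.21 and 1.07 respectively.

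**3. The same contrast with all 88 followed up.** SE = √[2 × 2(1 − ρ)/44], which is 0.2132, 0.2523 and 0.1651 for ρ = 0.5, 0.3 and 0.7. Multiplied by 2.834, these give 0.604, 0.715 and 0.468.

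**4. Mixed model with baseline means constrained equal.** The difference in change is then the baseline-adjusted difference at month 6. Its variance is approximately that of step 1, so power stays at about 80%.

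| ρ | Stated d | Power, step 2 | Detectable d, step 2 | Power, step 3 | Detectable d, step 3 |
|---|---|---|---|---|---|
| 0.5 | 0.572 | 70% | 0.65 | 75.6% | 0.604 |
| 0.3 | 0.63 | 64% | 0.76 | 69.5% | 0.715 |
| 0.7 | 0.472 | 74% | 0.51 | 80.7% | 0.468 |

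A complete-data simulation (20,000 replicates, 88 participants) gave 75.7%, 69.5% and 80.8% for the change contrast, in agreement with step 3.

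**The case against.** A reader might infer that the design cannot deliver 80% power at the stated effects. The documents do not support that, for two reasons.

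- **The model is not fully specified.** The analysis section names only terms that involve time and no component effect at baseline. A mixed model in which components enter only through time is the constrained model of step 4, and it loses nothing against ANCOVA. The unconstrained model is the ordinary reading, but it is not stated. A condensed article may leave this detail to the full protocol or analysis plan.
- **Attrition may be lower than planned.** The Results section can be read as reporting that all 88 randomized participants completed the 6-month follow-up. In that case the stated effect is met at ρ = 0.7, which the article calls the more realistic value, even under the unconstrained model.

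The consequences are also limited. The article says the study is not meant as a definitive, well-powered trial, and its Outcomes section makes feasibility primary and HbA1c secondary. The 88 are justified by pilot-size guidance, and power is presented for that number afterwards. A component is called active on a 0.5-point mean reduction in HbA1c, not on a significance test. The unconstrained contrast remains unbiased under randomization.

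These arguments lower the severity and make the shortfall conditional. They do not remove the mismatch: the article states both a power basis and a model, and as written the two do not correspond. Full follow-up does not close the gap at ρ = 0.5 or 0.3.

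**Conclusion.** The power statement and the planned analysis refer to different models. If component means are free at baseline, 15% are lost and all 88 baselines are used, the shortfall at the stated effects is about 10 points at ρ = 0.5, 16 at 0.3 and 6 at 0.7. With complete follow-up it is about 4 and 10 points at ρ = 0.5 and 0.3, and there is none at 0.7.

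Under that same model, the claim of power for still smaller effects fails at ρ = 0.5 and 0.3 even with no attrition (0.604 against 0.572, and 0.715 against 0.63). At ρ = 0.7 the gain is negligible (0.468 against 0.472).

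If baseline means are constrained equal, there is no shortfall. The result is therefore an inconsistency with a conditional loss of precision, not a demonstrated power failure. It should be fixed, but the pilot's primary aims do not depend on it.

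**What to change.** Before the effectiveness analysis, specify one of two models:

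1. Month-6 HbA1c regressed on baseline HbA1c, the two effect-coded factors and their product.
2. A linear mixed model with baseline and month 6 as outcomes and no component terms at baseline.

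Either makes the stated detectable effects correct for 74 followed up and gives narrower confidence intervals on the same data. The cost is one line of model specification; baseline HbA1c is already collected and no further participants are needed. The article describes the analysis as still to be completed, so the choice should be dated and recorded as made without sight of results by condition.

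If the unconstrained model is kept, restate the detectable effects as about 0.65, 0.76 and 0.51 for ρ = 0.5, 0.3 and 0.7 (0.97% HbA1c at ρ = 0.5), and drop the claim of power for even smaller effects.

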### Baseline Assessments

Once participant eligibility is confirmed from screening, the blood values used in the in-person screening visit described above are used as baseline values. In addition, a baseline survey packet consisting of sociodemographic questions and five validated survey instruments is sent electronically to the participants. The survey instruments are as follows: The Spoken Knowledge in Low Literacy in Diabetes Scale (SKILLD) assesses patients’ understanding of diabetes management [42]; the Patient Health Questionnaire-4 screens for symptoms of anxiety and depression [43]; The Diabetes Distress Scale measures the emotional burden associated with diabetes management [44]; The Diabetes Empowerment Scale evaluates patients’ self-efficacy in controlling diabetes [45], and the EQ-5D [46] survey assesses health-related quality of life. All study data are collected and securely stored in the REDCap database. If participants are unfamiliar or uncomfortable with completing the survey packet electronically or if they lack an email address, the survey packets are mailed to their preferred address. Included in the packet is a prepaid stamped envelope to return the survey packet. Upon receipt, survey responses are uploaded to REDCap, and the physical copies are stored in a secure cabinet at the research site.

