### Delivery of the Pedometer, Glucometer, and Educational Packet

Before the intervention began, participants across all arms of the study were shipped a pedometer, a glucometer with strips for 6 months, and a T2DM educational packet. The education content is highly pictorial and is based on the Diabetes Literacy and Numeracy Education Toolkit [47], a packet designed with low-literacy principles and visual aids, for T2DM education and management in patients with low literacy and numeracy skills. In addition, educational patient handouts from the Centers for Disease Control and Prevention (the National Diabetes Education Program and Diabetes Prevention Program) corresponding to all content areas measured by the SKILLD were included in the packet [48]. Topics covered in these materials included special considerations for exercise, understanding HbA_1c_, eye health, foot exams for individuals with T2DM, and visual aids for making healthy food replacements to manage blood sugar. A guide for estimating portion sizes was also included to facilitate accuracy with daily diet tracking. Sending the educational packet ensures that all participants have access to the same basic principles of diabetes management before starting the intervention.

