### Randomization

Computer-generated randomization assignment was done for all consented participants. We implemented a permuted block randomization with varying block sizes, blinded to the assessment team. Participants were randomized to four experimental conditions based on a 2 by 2 factorial design with equal probability allocation. The randomization list is concealed within the REDCap randomization module. We have programmed this such that the participant can be randomized and allocated only to an experimental condition after it is confirmed that baseline data have been collected and entered. Once the primary outcome measures are entered in REDCap, the study staff members can assign the participants to their respective experimental conditions. The statistician and the Principal Investigators are blinded, but the participants and the health coach are not blinded. All participants enrolled in the study were randomized to one of the four arms:

Arm 1: Adaptive reward+weekly automated coachingArm 2: Adaptive reward+weekly human coachingArm 3: Fixed reward+weekly automated coachingArm 4: Fixed reward+weekly human coaching

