### Intervention Components

#### Automated Behavioral Monitoring System

All participants receive daily calls through the ABMS using IVR technology for a 24-week period. Each participant selects a preferred call time during their initial orientation session with a health coach. If a call is missed, the system automatically places a reminder call 30 minutes later. Participants who miss both calls can return the call at their convenience to record their data.

Unlike traditional self-monitoring approaches that rely on written logs or mobile apps, the ABMS enables participants to speak naturally during calls—for example, “For breakfast, I had a muffin, a banana, and a cup of coffee” or “Today I walked about 5000 steps.” The system captures and processes this information seamlessly using AI-assisted NLP and nutrition databases. The ABMS is designed to collect daily data on four key self-management behaviors: dietary intake, PA, medication adherence, and fasting blood glucose monitoring (yes or no). Figure 3 outlines the 8-step structure of the ABMS used to support diabetes self-management in this study.

During the daily IVR calls, participants report their PA (eg, pedometer step count and engagement in moderate or vigorous activity), medication adherence (eg, whether medications were taken, taken as prescribed, and at the correct time), fasting blood glucose monitoring (yes or no), and dietary intake (meal-specific foods and beverages, including quantities). Textbox 2 lists the daily monitoring questions delivered by the IVR system, and the full branching logic is detailed in Multimedia Appendix 1.

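### The label 'active' is set on a fall from baseline, not on the randomized difference between component levels, so a fall shared by all arms can earn it

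*Protocol article*

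**What the plan says.** Under Analytic Strategy for Preliminary Effectiveness Analyses, the plan uses linear mixed models and states that "these effects will be statistically modeled as component-by-time interactions, with the 6-month outcome as the primary end point". It adds the interaction between the two factors and time, and plans 75%, 85% and 95% confidence intervals. The next step is "We will then identify all the active components or combinations of components". The criterion for that label on HbA1c comes in the same sentence: "where active is operationalized as a mean reduction of 0.5 units (%) in HbA_1c_ between baseline and month 6". For weight, "an average 5% weight loss is considered to be active in the case of weight". Neither threshold names a reference level or refers back to the interaction estimate.

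The design around this rule is as follows.
- Randomization: "Participants were randomized to four experimental conditions based on a 2 by 2 factorial design with equal probability allocation". The factors are adaptive versus fixed reward and automated versus human coaching. Both levels of each are delivered; none is untreated.
- Automated Behavioral Monitoring System: "All participants receive daily calls through the ABMS using IVR technology for a 24-week period".
- Delivery of the Pedometer, Glucometer, and Educational Packet: "participants across all arms of the study were shipped a pedometer, a glucometer with strips for 6 months, and a T2DM educational packet". The following section gives every participant a personalized orientation session.
- Baseline Assessments: "the blood values used in the in-person screening visit described above are used as baseline values". Entry requires HbA1c from 6.5% to 11.5%, so the value that qualifies a participant is also the baseline.

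**The concern.** The analysis estimates one quantity and attaches its label to another. The component-by-time term is the difference in change between two randomized levels, so anything common to both levels cancels. A mean fall from baseline does not have that property. It adds together the level's own contribution, the effect of the core package, any change in usual care over six months, and regression to the mean from reusing the qualifying HbA1c as baseline.

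Every arm receives a package intended to lower HbA1c, so a shared fall is plausible whether or not the choice of coaching or reward matters. Under the literal rule such a fall counts towards the label. Both levels of a factor can then be called active, which says nothing about which to prefer, or one level can be called active and the other not by chance. What is at stake is the study's stated conclusion about which components or combinations are active on HbA1c and weight.

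**Working it through.** **The plan's own figure.** Sample Size Justification gives 80% power at d = 0.572 for correlation 0.5, 15% attrition and type 1 error 0.05 (taken as two-sided). With 37 completers per level, the normal approximation is (1.960 + 0.842) × √(1 − 0.5²) × √(2/37) = 0.564, and the noncentral t gives 0.572. Then 0.572 × 1.5 = 0.858, the stated 0.86% units. The figures for correlations 0.3 and 0.7 (0.63 and 0.472) also reproduce. This power statement concerns a between-level difference, which is not the quantity in the 0.5 rule.

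**The rule as written, with no component effect.** Inputs from the article are SD 1.5, correlation 0.5, and 44 per level or 22 per cell. The Results section reports that 88 participants completed follow-up; with the planned 15% attrition the numbers would be 37.4 per level and 18.7 per cell. The shared fall is my assumption, because the article gives none.

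- SD of change = 1.5 × √(2(1 − 0.5)) = 1.5.
- P(a level qualifies) = Φ((fall − 0.5) / (1.5/√n)). For a fall of 0.3 and n = 44: SE = 0.226, z = −0.88, P = 0.19. For n = 37.4: SE = 0.245, P = 0.21.
- The two levels of a factor contain different participants, so P(both qualify) = P².
- P(at least one of four cells qualifies) = 1 − (1 − p)⁴, with p the cell probability. For a fall of 0.3 and 22 per cell: SE = 0.320, p = 0.266, giving 0.71. For 18.7 per cell: p = 0.282, giving 0.73.

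| Assumed shared fall (% HbA1c) | A given level qualifies | Both levels of one factor | At least one of four cells |
|---|---|---|---|
| 0 | 1–2% | about 0% | 22–27% |
| 0.3 | 19–21% | about 4% | 71–73% |
| 0.5 | 50% | 25% | 94% |
| 0.7 | 79–81% | 63–66% | 99% |

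The chance that exactly one level of a factor qualifies is 2P(1 − P): about 31–33% at a shared fall of 0.3 and 50% at 0.5. Over correlations 0.3 to 0.7 the row for 0.5 is unchanged. At a shared fall of 0.3, a given level qualifies 13–24% of the time and at least one cell 61–78%.

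**The same threshold on the randomized contrast.** With a true difference of 0 and correlation 0.5, the ANCOVA SE is 1.5 × √0.75 × √(2/44) = 0.277, so an observed difference of at least 0.5 favouring a named level occurs in 3.6% of trials (4.8% at 37.4 per level). On change scores it is 5.9% to 7.5%. These figures do not depend on the shared fall. Power to detect a true difference of 0.5 (d = 0.5/1.5 = 0.33) is about 37–43% at correlation 0.5, and 32–58% over 0.3 to 0.7.

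**Regression to the mean, as illustration only.** The expected fall is (1 − r) × (mean of those admitted − population mean). Assume a population SD of 1.5, truncation at 6.5–11.5 and r from 0.9 to 0.5. A population mean of 7.0 gives an admitted mean of 7.89 and a fall of 0.09 to 0.44. A mean of 8.0 gives 0.04 to 0.19, and a mean of 9.0 gives 0. The article supplies none of these inputs, so regression to the mean is a possible contributor of unknown size.

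**The case against.** The strongest reply is that the threshold follows directly after the component-by-time model, so the mean reduction may be meant as the modelled effect. That reading is possible, and the rule also cites sources that are not available here. But no sentence ties the threshold to the interaction estimate, and the weight example is worded as an average loss, which points to change within a group. If the contrast is intended, one sentence settles it.

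A second reply is that little depends on the label. Much of this stands. A reader might infer that the label decides which components enter the optimization trial, but the article says only that active components will be identified; no passage keeps or drops a component on this basis. A reader might also infer that the benefit of the factorial randomization is lost. It is not, because the randomized contrasts and their intervals are still estimated and reported.

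Third, the size rests on an assumed shared fall. That is correct, and the row for a shared fall of 0 belongs in the picture: a given level then qualifies only 1–2% of the time, although some cell still does in 22–27%.

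Finally, automated coaching is proposed as a scalable, low-cost alternative to human coaching, so near-equality could be a favourable result. A rule that asks for a 0.5 advantage would not show this. That is a real cost of the remedy, and a reason to keep the pre-post result as description.

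**Conclusion.** The point holds in limited form. Read literally, the label applies to a pre-post change without a comparator, in a design where all arms share the core package and no level is untreated. A shared fall can therefore be credited to a component, or to both levels of one factor, when the levels do not differ. The problem is small for single levels if the shared fall is near 0 and large from about 0.5 upward. The calculation assumes SD 1.5, correlation 0.5, normally distributed cell means and an equal fall in all arms; the documents do not state the size of that fall.

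The Outcomes section and Table 2 make feasibility primary and HbA1c secondary, although the abstract lists preliminary HbA1c change among the primary outcomes. On the Outcomes section's classification, the feasibility results are untouched and only the conclusion about active components is affected. This is a should-fix point. A higher rating would need a stated use of the label to select components, which the article does not contain.

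**What to change.** Apply the threshold to the baseline-adjusted difference between the two levels of each factor at month 6, that is, the component-by-time estimate, with the interaction used for combinations. Name the reference level of each factor. Report the estimate with the planned 75%, 85% and 95% confidence intervals against 0.5% HbA1c, and present it as estimation, given the power of about 37–43%. Treat weight in the same way. Whether a level or combination reaches a 0.5% fall in HbA1c or a 5% weight loss from baseline may still be reported, as a descriptive result for the whole package that is not attributable to a component.

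The cost is wording in the analysis plan; no new data are needed. Follow-up is reported as complete and analysis was expected to finish by December 2025, so the definition should be settled before results are interpreted. The downside is that fewer components will be labelled active, and similarity of automated and human coaching must be read from the confidence interval instead of the label.
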